# Data and Specimen Banking*

- 1. N/A – no specimens will be taken or stored in this study
  2. All original copies of collected data including demographics, consent and liability waivers, functional outcome assessments, and completed Daily Activity Logs, will be stored in a secured and locked cabinet on hospital property. Electronic data and recorded videos and stored on encrypted password-secured hard drives that will be kept in a locked cabinet on hospital property. Access to study documentation and data will be limited to investigators listed on the IRB.

# Sharing of Results with Subjects*

- 1. Pre- and post-study assessment results may be shared with family upon request, at the completion of the study. They will be shared with the family verbally or through secured email correspondence.

# Study Timelines*

- 1. Data will be collected for a period of up to 2 years, with subjects enrolled in the interventional period for a duration of 6 months. Data collection of functional outcomes will occur at baseline, a midpoint assessment, and final visit at month six, +2 weeks for each timepoint.
  2. We anticipate all subjects be enrolled within one year of study start date and anticipate completion of study including primary analysis to be complete within two years of the study start date.

# Inclusion and Exclusion Criteria*

- 1. Subjects will be screened during regular clinic visits, by review of inclusion/exclusion criteria in correspondence with family, and/or prior to enrollment and informed consent process.
  2. **Inclusion criteria:** Able to safely fit in pediatric harness; genetic diagnosis of spinal muscular atrophy, delay in standing or walking, able to right head from full flexion, treatment with a disease modifying agent

**Exclusion criteria:** At any point during interventional period of the study, a body weight greater than 50 pounds (lbs) or 22.68 kilograms (kg); evidence of current or previous unresolved lower limb injury, current or recurrent fractures within the past 6 monhts that could affect performance or study procedures; medical condition or developmental history (i.e. concomitant illness, behavioral disorder, prematurity, uncontrolled seizure disorder) that in the opinion of the investigator, make it unsafe for the subject to participate or could impair study results

- 1. We will include individuals who are not yet adults (infants and children).

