# Study Summary

| **Study Title** | Exploring the feasibility and utility of in-home body weight support harness system use in children treated for spinal muscular atrophy |
| --- | --- |
| **Study Design** | Pilot interventional study |
| **Primary Objective** | Investigate whether BWSS is a feasible option for in-home exercise and investigate the use of home-based functional exercise using a body weight support harness system (BWSS) on motor performance in children treated for spinal muscular atrophy |
| **Secondary Objective(s)** | Explore influence of frequency of use on change in motor performance over 6 months. |
| **Research Intervention(s)/ Investigational Agent(s)** | Enliten, LLC portable body weight support harness system (BWSS) |
| **IND/IDE #** |  |
| **Study Population** | Children who have been treated for spinal muscular atrophy |
| **Sample Size** | Up to 50 children |
| **Study Duration for individual participants** | On-going; each child will be followed for six months with possibility of extension. |
| **Study Specific Abbreviations/ Definitions** | BWSS – body weight support harness system  SMA – spinal muscular atrophy |

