Families will be given the option to complete the midpoint functional assessments during an in-home visit or during a regularly scheduled clinic or research appointment at NCH. Midpoint assessment visits may also occur remotely using approved video conferencing services. Photos and videos of the child performing motor skills will be accepted to incorporate into the midpoint assessment up to one week after the date of visit. Photo and video submissions will only be accepted for assessments performed remotely.

**Final Visit**: A study team member will complete final functional outcome assessments. Families will be given the option to complete the final functional assessments during the in-home visit or during a regularly scheduled clinic or research appointment at NCH. Final assessment visits may also occur remotely using approved video conferencing services. Photos and videos of the child performing motor skills will be accepted to incorporate into the final assessment up to one week after the date of visit. Photo and video submissions will only be accepted for assessments performed remotely.

Families will be provided with an opportunity to enter the Optional Enrollment Extension phase (see 6.2.1 point below).

If the family would like to continue enrollment but the BWSS is already assigned to another subject on the waitlist, the Final Visit will be completed as detailed in 9.2.1 and the family will be placed on the waitlist for re-enrollment.

6.2.1 **Final Visit - Optional Enrollment Extension:** Should the family choose to continue enrollment following the 6-month finial visit, the BWSS will remain in the family’s home until the family withdraws from the study or until BWSS equipment is needed for use with another subject.

Families will be asked to continue documenting BWSS use in Daily Activity Logs. Functional assessments may be performed, either in the home or during a regularly scheduled clinic or research appointment at every 6-9 months.

6.2.2 **Final Visit without Enrollment Extension:** A study team member will return to the family’s home to dismantle the BWSS unit. Prior to disassembly, a final equipment check using the BWSS safety Inspection Check List will be completed, reviewed, and signed by the study team member and responsible parent. Daily activity log will be checked and completion will be documented

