- 1. All functional outcome assessments will be video recorded. Parents may also submit video evidence of motor skill attainment within 7 days of any remote study visit, should the child not perform on the date of the assessment due to child’s mood or behavior.
     - Parents will submit video evidence through secured email communication. Submitted videos will be stored on secured NCH research drive, alongside other assessment videos.
  2. FFamilies will be educated on appropriate activities to help engage with their child in the harness.

Each family will receive an Activity Ideas booklet to reference throughout the duration of the study (Appendix F).

- 1. Families will be asked to fill out the Daily Activity Log (Appendix G) each time the harness is used. The log will include information on the duration and frequency of BWSS use, activities completed with child while in BWSS, and any observed changes in child’s motor function
  2. Families may be asked to attach a motion sensor to the harness system.
  3. **Liability Waiver and Legal Agreement**: Families are to review and sign a liability waiver prior to in-home equipment set-up. This documentation to be created by Nationwide Children’s Hospital Corporate Legal Services department and addresses the expectations and responsibilities of the families to maintain the integrity of the BWSS for the duration of the study
  4. **Safety Considerations**
     - **Equipment Inspection**
       - Equipment will be required to pass study team member inspection using the BWSS Inspection Checklist provided by Enliten, LLC. (Appendix A)
       - Equipment safety checks will occur at screening (prior to in-home set up), baseline, and final visit. Photographs or video of in-home set up will be included in safety documentation.
       - It will be required that the BWSS Inspection Check List be completed by the study team member and reviewed and signed-off by the study team member and parent at baseline and final study visit.
     - **Adult Supervision**
       - Families are required to supervise their child while using the BWSS at all times.
     - **Family Training**

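### The 50 lb weight limit is written for the six-month interventional period only, so no numeric limit clearly applies when the harness stays in the home during the extension

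*Protocol*

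**What the plan says.** The exclusion criteria in the Protocol's Inclusion and Exclusion Criteria section include "At any point during interventional period of the study, a body weight greater than 50 pounds (lbs) or 22.68 kilograms (kg". It is the only numeric body-weight criterion in the protocol.

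Study Timelines defines the period it refers to, "with subjects enrolled in the interventional period for a duration of 6 months". The Study Summary describes individual duration more loosely: "each child will be followed for six months with possibility of extension".

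Under Procedures Involved, section 6.2.1 (Optional Enrollment Extension), a family that continues keeps the BWSS "until the family withdraws from the study or until BWSS equipment is needed for use with another subject". Activity logs continue. On contacts, the section says only: "Functional assessments may be performed, either in the home or during a regularly scheduled clinic or research appointment at every 6-9 months". It names neither a weight nor a weight limit.

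Three general safeguards carry no time limit:
- Withdrawal of Subjects lets the principal investigator (PI) withdraw a child judged unsafe in the device at any time, and gives a change in the child's build or health as an example.
- Safety Considerations states: "Families are required to supervise their child while using the BWSS at all times".
- Family Training tells families not to use the system if they have a safety concern.

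**The concern.** The criterion covers the whole interventional period, so it acts as a continuing-use rule and not only as an entry rule. The sponsor evidently meant it to hold while the child uses the device. Yet it is tied to a named period of fixed length, and the protocol then allows use of the same device beyond that period with no stated maximum.

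Nothing in the protocol suggests that the reason for the 50 lb figure ends at month six, and children can be expected to gain weight. At stake is whether staff know that a child who passes the limit in the extension must stop, and whether any planned contact would show that the limit had been passed.

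**Working it through.** **The stated figure.** 50 lb × 0.45359237 kg/lb = 22.6796 kg, which rounds to 22.68 kg. The two units agree, so the fault is in the scope of the limit and not in its value.

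**Scope, with the sections side by side.**

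| Question | Six-month period | Extension |
| --- | --- | --- |
| Numeric weight limit stated? | Yes, 50 lb (Inclusion and Exclusion Criteria) | Not clearly |
| Length | 6 months (Study Timelines) | Open-ended (6.2.1) |
| Stop condition based on weight? | Yes, through the criterion | None; only family withdrawal or need for the unit elsewhere |
| Weight named at a visit? | No, though the criterion implies one | No |
| PI may withdraw an unsafe child? | Yes | Yes |

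**The two readings.**
1. Literal reading: Inclusion and Exclusion Criteria plus Study Timelines give a limit that ends at month six. Section 6.2.1 does not renew it.
2. Favourable reading: the Study Summary treats the extension as a continuation of follow-up, and the device and log are the same. The limit would then carry forward.

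The explicit 6 months in Study Timelines favours the first reading, but the text does not settle the matter. Even on the second, no weight is scheduled that would show that a child had crossed the limit.

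**How long the gap could last.** Section 6.2.1 sets no maximum. Study Timelines expects all enrolment within one year and says the sponsor "anticipate completion of study including primary analysis to be complete within two years of the study start date". On that timeline:
- child enrolled at month 0: 24 − 6 = 18 months of extension;
- child enrolled at month 12: 24 − (12 + 6) = 6 months of extension.

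The 18 months is an extreme bound. It needs enrolment on the first day and device use up to the end of the two years, which also have to contain the primary analysis. Extensions also end when a child on the waitlist needs the unit.

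**The case against.** The strongest reply is that this is a wording ambiguity already covered by judgement. No sentence permits a child over 50 lb to continue. The PI's power to withdraw runs for the whole study, and its example of a changed build fits a child who outgrows the device. Supervision and the instruction to stop when concerned also continue. All of this stands, and it keeps the point minor. What remains is that none of these provisions gives a number, none is prompted by a scheduled weight, and nothing in the protocol text tells families that passing 50 lb is a reason to stop.

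The inspection checklist, the instruction manuals and the manufacturer's safety information are in appendices that are not shown, and they may contain a user weight limit. That also stands. The protocol's own criterion would still need to agree with them.

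A reader might infer three stronger points that the documents do not support:
- *A child over 50 lb is in danger from overloading.* Study Intervention/Investigational Agent gives 50 lb as the support that the springs supply. It is not stated as a load limit.
- *The extension is less well inspected than the main period.* The checklist is "reviewed and signed-off by the study team member and parent at baseline and final study visit", so month six is covered. The main six months also has no scheduled inspection between baseline and final visit, and names no weight. A six-month extension therefore leaves about the same interval that the protocol already accepts.
- *A given number of children will cross the limit.* The protocol gives no weights and no growth figures, so the number could be zero.

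**Conclusion.** The point holds as a minor fault of scope. The 50 lb limit is stated for a six-month period, while device use may continue beyond it with no stop condition based on weight. Because of the Study Summary the text is ambiguous rather than plainly permissive. In the extension, PI discretion and family caution are the only cover that the protocol text provides.

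The conclusion assumes that the interventional period means the 6 months in Study Timelines, and that the appendices do not already set a limit for continued use. If they do, the fix reduces to bringing the protocol into line with them.

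There is no effect on the planned comparison of baseline and final visit scores, which ends at month six. How many children are affected cannot be estimated from the documents.

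**What to change.** 1. In Inclusion and Exclusion Criteria, state that body weight must be at or below 50 lb (22.68 kg) at screening.
2. In section 6.2.1 and in Withdrawal of Subjects, state that device use stops above 50 lb for as long as the BWSS is in the home, extension included.
3. Record a weight at the midpoint visit, the final visit and each 6-9 month extension contact. Accept a clinic or home-scale weight, so that remote contacts are covered. Extension assessments are optional as written, so ask for the weight even when no motor assessment is done.

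No extra inspection in the extension is needed for this point.

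**Cost.** A few sentences, plus two weights per child in the main period: 15 × 2 = 30 for the 15 children expected locally, or 50 × 2 = 100 at the maximum sample size. Each extension contact adds one more. The downside is slight staff time, and some families will have to stop using the device when the child passes 50 lb.

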# Vulnerable Populations*

- 1. The research subjects will be minors. HRP-416 has been consulted. Consenting procedures are as follows:
     - The child’s parent or guardian will provide written informed consent according to institutional guidelines. If the child is over 7 years of age, they will provide written assent for participation. The study procedures, risks, and benefits to participation will be explained to the parent by a member of study staff. The parent will have the opportunity to ask questions and have their questions answered. If the subject and parent agree to participate upon full understanding of the study requirements, they will provide written informed consent.

# Local Number of Subjects

- 1. We expect 15 subjects to be enrolled locally.

# Recruitment Methods

- 1. Subjects will be recruited through Nationwide Children’s Hospital Spinal Muscular Atrophy clinic, through IRB approved flyers, and by word of mouth.

# Withdrawal of Subjects*

- 1. Participation in this study is optional for the family and subject; families are given the option to withdrawal at any time. Withdrawal from this study will not affect any care provided to the patient at Nationwide Children’s Hospital. Subjects may choose to withdrawal due to lack of time/scheduling conflicts, unrelated injury of subject, outside treatments that may affect BWSS use (i.e. surgery, serical casting, etc.)
  2. Final determination of family and subject eligibility is at the discretion of the PI. If at any point during the study, the patient is determined to be un-safe while in the BWSS (e.g. change in body type or health status, un-safe practices of family noted during in-home visits) the PI may withdrawal the family from the study
  3. If subjects are withdrawn from the study, they will be instructed to discontinue use of BWSS and a clinical evaluator will come to their home to disassemble harness system and complete final safety checks.

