# Study Endpoints

- 1. Primary endpoints for feasibility include using a 5-question Likert-style scale survey of patient reported experience and documented frequency and duration of BWSS use. Primary endpoints for utility are assessments of gross motor function and include The World Health Organization’s gross motor developmental milestones, Bayley Scales of Infant Development v.3 Gross Motor subtests, Hammersmith Functional Motor Scale Expanded and/or Revised, and Neuromuscular Gross Motor Outcome.

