# Procedures Involved*

- 1. This is a voluntary study investigating the feasibility and effects of a home-based functional exercise program using a body weight support harness system (BWSS) on motor performance in children treated for spinal muscular atrophy. Subjects will be provided with one portable BWSS, manufactured by Enliten LLC, to be used in their home for a period of 6 months. Subjects will engage in a BWSS use and document frequency / duration of use.
  2. **Screening/Baseline**: Subject demographic information and equipment safety check will be completed prior to the initial in-home visit. Baseline assessment of motor function may be completed at any time within a 3 week window prior to or during the initial in-home visit.

**Initial Visit (in-home):** A study team member will travel to the subject’s home to complete the BWSS set up. The BWSS Inspection Check List will be reviewed and signed by the responsible participating family member and the study team member. Pictures or video of the final set-up will be taken and stored in the subjects file. The participating family members will be trained on how to securely strap their child into the harness and on appropriate activities to engage in with their child while in the harness. They will be instructed on frequency and duration of treatment time and asked to document this information in the Daily Activity Log. They may be asked to attach an activity monitor to the harness.

Prior to completion of this visit, the following documentation will be completed: 1) Informed Consent; 2) BWSS Inspection Check List; 3) Pictures or video of BWSS set-up in home.

A study team member will contact the family between the baseline and midpoint assessment visit to ensure the family is comfortable with BWSS use. If the family has questions or concerns, they will be addressed by the study team member via Skype or video conference phone call. If determined necessary by the PI, a study team member will travel to the family’s home for an additional in-home visit.

**Midpoint Assessment Visit**: A study team member will complete functional outcome assessments and evaluate compliance with usage schedule. Daily Activity Log will be checked and completion will be documented.

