# Data Management* and Confidentiality

- 1. Baseline and Final visit assessment scores will be compared. We will explore factors that may impact outcomes including reported frequency of use. Subjects may be stratified into groups based on such factors and sample group change averages will be compared.
  2. All source form data will be stored in locked cabinets in a locked office for the duration of the study. Electronic data entry will be stored on secured NCH research drive ([name]) and will be password protected.
  3. Data will be stored indefinitely
  4. Access to data: only investigators listed on IRB will be provided access to study materials.

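### Withdrawn children get a home visit with no motor assessment, so early withdrawals have no closing score for the Baseline–Final comparison

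*Protocol*

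**What the plan says.** Withdrawal of Subjects, item 3, has withdrawn families stop using the device, after which "a clinical evaluator will come to their home to disassemble harness system and complete final safety checks". Those are the only tasks listed for the visit.

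Motor function is a primary outcome: "Primary endpoints for utility are assessments of gross motor function" (Study Endpoints). The schedule is: "Data collection of functional outcomes will occur at baseline, a midpoint assessment, and final visit at month six" (Study Timelines, with a +2 week window). The analysis is described in Data Management and Confidentiality: "Baseline and Final visit assessment scores will be compared". The secondary aim is served by the same change scores: "Subjects may be stratified into groups based on such factors and sample group change averages will be compared".

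The feasibility endpoints in Study Endpoints are a "5-question Likert-style scale survey of patient reported experience and documented frequency and duration of BWSS use". At an ordinary take-down (Procedures Involved, 6.2.2) the Daily Activity Log is checked and its completion recorded. The withdrawal paragraph has no such step. No section assigns the survey to a visit.

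**The concern.** A member of the team goes to the home of each withdrawn child, yet the protocol does not use the visit to collect the outcome. What is not measured then cannot be recovered later by any analysis plan.

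The reasons given for withdrawal make chance loss doubtful. Families may leave for lack of time, an injury unrelated to the device, or outside treatment such as surgery or casting. The principal investigator may withdraw a child for a change in body type or health status, or for unsafe use. Several of these may relate to motor outcome. Lack of time may also go with low use, in which case the frequency-of-use comparison would lose part of the low end of its range. At stake is whether the reported mean change describes all children who started or only those who stayed.

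**Working it through.** **Step 1: which scores does a withdrawn child have?**

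| Time of withdrawal | Baseline | Midpoint | Closing score |
| --- | --- | --- | --- |
| Before midpoint | yes | no | none |
| Between midpoint and month six | yes | yes | none |
| Completes | yes | yes | Final Visit |

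The closing column follows from Procedures Involved, which places the last study-period assessment at the Final Visit, and Study Timelines, which sets that visit at month six. An early take-down is not a Final Visit. The midpoint column follows from Procedures Involved: "A study team member will complete functional outcome assessments and evaluate compliance with usage schedule". No use of the midpoint motor scores is stated in the comparison.

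**Step 2: how large could the effect be?** The protocol gives no dropout rate, effect size or SD, so there is no figure of its own to reproduce. What follows is an illustration.

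Inputs from the protocol: 15 children expected locally (Local Number of Subjects); up to 50 (Study Summary). Assumed inputs: the number withdrawn, and a mean change in withdrawn children that is 0.5 to 1.0 SD lower than in completers.

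Let d be the share withdrawn. The mean over all enrolled is (1 − d) × (completers' mean) + d × (withdrawn mean). Subtracting this from the completers' mean gives

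bias = d × (completers' mean − withdrawn mean).

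The standard error of the completers' mean, in SD units, is 1/√n with n completers.

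| Enrolled | Withdrawn | d | Bias at 0.5 SD | Bias at 1.0 SD | Standard error |
| --- | --- | --- | --- | --- | --- |
| 15 | 0 | 0 | 0 | 0 | 1/√15 = 0.26 |
| 15 | 2 | 0.133 | 0.07 | 0.13 | 1/√13 = 0.28 |
| 15 | 3 | 0.200 | 0.10 | 0.20 | 1/√12 = 0.29 |
| 15 | 5 | 0.333 | 0.17 | 0.33 | 1/√10 = 0.32 |
| 50 | 5 | 0.100 | 0.05 | 0.10 | 1/√45 = 0.15 |
| 50 | 10 | 0.200 | 0.10 | 0.20 | 1/√40 = 0.16 |
| 50 | 15 | 0.300 | 0.15 | 0.30 | 1/√35 = 0.17 |

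A simulation of 20,000 trials of 15 children, with an assumed correlation of 0.5 between motor change and a latent tendency to stay, gave mean biases of 0.09, 0.17 and 0.27 SD at 10%, 20% and 33% withdrawal. These fall within the ranges that the formula gives for those shares.

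**Step 3: feasibility.** Families fill in the log each time the harness is used, and logs are checked at midpoint, so usage before withdrawal is recorded. Not secured are the check of the log at take-down and the survey.

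**The case against.** The strongest reply is that this is an exploratory pilot with no stated hypothesis test, and that the analysis set and missing-data handling are commonly left to a statistical analysis plan, which is not at hand. That stands for the analysis: a mixed model or a completer definition need not be in the protocol. It does not answer the missing assessment, which is a matter of data collection. The reply is also right that a score taken at early withdrawal is not a month-six score, so collecting it reduces the bias without removing it.

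A reader might infer more than the text supports:

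- That the analysis uses Baseline and Final scores alone. Data Management and Confidentiality names these two visits but does not bar midpoint scores.
- That families for whom the device failed vanish from both primary results. Logs kept before withdrawal can still inform feasibility, and no section limits feasibility to completers.
- That withdrawal means failure of the device. The listed injury is an unrelated one, and scheduling conflicts or outside surgery do not show failure either.
- That children who pass the weight limit are dropped from the data. The criterion reads "At any point during interventional period of the study, a body weight greater than 50 pounds", but nothing says that data already collected are discarded, and how many would cross the limit is unknown.

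**Conclusion.** The point holds for the motor endpoints and for the comparison of change by frequency of use: a child withdrawn before month six contributes no closing score, and the loss may be selective. For feasibility it is a smaller gap, confined to the log check at take-down and the unscheduled survey.

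The size cannot be derived from the protocol. Under the assumed 0.5 to 1.0 SD deficit, 2 withdrawals among 15 give a bias well below the standard error, while 5 can give one as large as the standard error (0.33 against 0.32 SD). If withdrawn children change as much as completers, or if none withdraw, there is no bias. This is a cheap improvement worth making before more children withdraw, not a flaw that invalidates the study.

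**What to change.** In Withdrawal of Subjects, item 3, add that, where the family agrees and it is safe for the child, the evaluator completes the functional assessment at the existing take-down visit, or the study team does it remotely as Procedures Involved already allows for midpoint and final visits. At the same visit the 5-question survey is given and the Daily Activity Log collected.

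In Data Management and Confidentiality, add that the available midpoint and withdrawal scores of children without a Final score will be used, or reported with their dates, alongside the Baseline–Final comparison, and that feasibility is reported for all enrolled families. The choice of model can stay with the statistical analysis plan.

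Cost: a protocol amendment and a somewhat longer visit that takes place anyway. The withdrawal scores will come at varying times and must not be read as month-six scores, and the feasibility figures may look less favourable.
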